**Fig. 1 Fig1:**
[figure not shown]
Schematic overview of the study design. Note: Each module includes three sessions

### Sample size

The trial is well powered with *n* = 64 in each of the four conditions (*n* = 256 in total) to detect a clinically relevant effect (mean standardized difference, *d*) of *d* ≥ 0.33 as statistically significant (at α ≤ 0.05, 2-tailed) with a power of (1-β) ≥ 0.80 when the primary outcome (depressive symptoms) is evaluated in a baseline adjusted analysis of variance (ANCOVA) while also taking into account the nesting in the data owing to the cluster randomized trial.

More specifically, the power calculation was conducted using Stata’s 14.2 sample size procedure (*sampsi*) assuming that the evaluation would be carried out in a baseline adjusted ANCOVA with one baseline assessment and one follow-up (*t*_*1*_). The correlation (*r*) between *t*_*0*_ and *t*_*1*_ (*r* = .80) was estimated from preliminary data. This indicated that 52 respondents per condition were required. In a next step, we calculated the design effect of 1.22 while taking into account the intraclass correlation coefficient (*icc*), the mean cluster size (*m*), the coefficient of variation (*cv*) of the cluster sizes. The *icc* was estimated at 0.05, *m* and *cv* where estimated from preliminary data at 5 and 0.30, respectively. Hence, 64 (52*1.22) participants per condition are needed or a total *n* of 256. We will not increase the sample size at baseline to compensate for dropout, because all analyses will carried out in agreement with the intention-to-treat principle.

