The study also has limitations. We will not include a control group, limiting the extent to which a decrease in depressive symptoms in the four intervention groups can be uniquely ascribed to the prevention program. The reason for this is that several meta-analyses and reviews have already established the superior effect of CBT in comparison to waitlist and placebo (e.g., [81–83]). Another limitation is the design of a cluster randomized trial, because of the great risk on baseline imbalance between study arms [84]. We will try to reduce this risk by stratifying students by gender and age. The study’s power is also a limitation. Although the study is well powered on the main effects, the power might be too low for conducting moderation analyses. Therefore, these analyses will be done exploratory. At last, given previous prevention trials, we expect a high number of dropout in both the assessment and intervention phase, which will have consequences for the effectiveness [85]. In order to motivate adolescents to participate in the assessments, we will provide incentives for participation. Besides, all treatment drop-outs will be asked to complete the post- and 6-month follow-up assessments. To prevent the effect of dropout on the effectiveness, all analyses will be conducted according to the intention-to-treat principle.

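### Intention-to-treat is given as the reason for no dropout allowance although high dropout is expected; power of at least 0.80 needs virtually every t1 score to be observed

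*Protocol article*

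**What the plan says.** The Sample size section of the protocol article bases power on a baseline-adjusted ANCOVA with one follow-up, t1, which falls after the first three-session module. It claims to detect d of 0.33 or more "at α ≤ 0.05, 2-tailed" and "with a power of (1-β) ≥ 0.80". On the calculation before clustering it reports: "This indicated that 52 respondents per condition were required". Multiplying by a design effect of 1.22 gives 64 per condition, 256 in all. On dropout it says: "We will not increase the sample size at baseline to compensate for dropout, because all analyses will carried out in agreement"; the sentence ends by naming intention-to-treat.

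The Recruitment, screening and randomization section ends screening when 256 is reached.

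The Strengths and limitations section says "we expect a high number of dropout in both the assessment and intervention phase". It closes the topic with "To prevent the effect of dropout on the effectiveness, all analyses will be conducted according to the intention-to-treat principle". The same paragraph calls the study well powered on its main effects.

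**The concern.** The stated reason does not support the decision. Intention-to-treat is a rule about the analysis set: everyone randomised is kept, in the arm to which they were randomised. An adolescent whose CDI-2 at t1 is missing still belongs to the arm but brings no observed t1 outcome, so the information behind the t1 contrast shrinks whatever the analysis set is called.

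This matters because the plan itself expects dropout from the assessments, not only from the sessions, and because the sample size leaves almost no margin. A non-significant difference between components would be read as coming from a trial with 80% power when the real figure may be clearly lower. The second sentence, in Strengths and limitations, also tells readers that the effect of dropout has been dealt with by a principle that does not deal with it.

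**Working it through.** **Inputs, all from the Sample size section:** d = 0.33; two-sided alpha 0.05; power 0.80; correlation between t0 and t1 r = 0.80; ICC 0.05; mean cluster size m = 5; coefficient of variation of cluster size cv = 0.30.

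**Step 1. Reproduce the plan's figure.**

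- Residual SD after baseline adjustment: √(1 − 0.80²) = 0.60.
- n per condition before clustering: 2 × [0.60 × (1.960 + 0.842) / 0.33]² = 51.9, so 52. This agrees with the plan.
- Design effect: 1 + [(cv² + 1)m − 1] × ICC = 1 + (1.09 × 5 − 1) × 0.05 = 1.2225. The plan gives 1.22.
- 52 × 1.22 = 63.4, rounded up to 64. This agrees with the plan.

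**Step 2. Power with complete t1 data.**

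- Effective n = 64 / 1.2225 = 52.35.
- Standard error = 0.60 × √(2 / 52.35) = 0.1173.
- Power = Φ(0.33 / 0.1173 − 1.960) = Φ(0.854) = 0.803.

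The margin over 0.80 is only the rounding.

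**Step 3. Power with a fraction p of t1 scores missing.** Observed n per arm is 64(1 − p). The design effect is either held at 1.2225 or recomputed with mean observed group size 5(1 − p), which is more lenient. For p = 0.10, the recomputed value is 1 + (1.09 × 4.5 − 1) × 0.05 = 1.195. Detectable d at 80% power is (1.960 + 0.842) × 0.60 × √(2 × DE / n).

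The article gives no dropout rate, so every p above zero is an assumption.

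| t1 scores missing | Observed n per arm | Power at d = 0.33, DE fixed | Power, DE recomputed | Detectable d, DE recomputed to fixed |
|---|---|---|---|---|
| none | 64 | 0.803 | 0.803 | 0.329 |
| one per arm (1.6%) | 63 | 0.797 | 0.799 | 0.331 |
| 5% | 60.8 | 0.783 | 0.788 | 0.335 to 0.337 |
| 10% | 57.6 | 0.761 | 0.770 | 0.342 to 0.346 |
| 20% | 51.2 | 0.711 | 0.731 | 0.359 to 0.367 |
| 30% | 44.8 | 0.653 | 0.683 | 0.379 to 0.393 |

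Power crosses 0.80 at about 1% loss. A shortfall of more than two percentage points (power below 0.78) appears from about 6% loss with the design effect fixed and about 7.5% with it recomputed.

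**The case against.** Several things can fairly be said for the plan.

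- **t1 is early.** The power statement concerns the assessment after three sessions, held once or twice a week. The expected high dropout is described for the assessment and intervention phases as a whole, and no rate is given for t1. Loss at t1 may well be smaller than at t4 or t5, and leaving the sessions does not by itself lose an outcome. This stands: the size of the shortfall is not known. It does not rescue a zero allowance, since one missing score per arm already uses up the margin.
- **Mitigation is planned.** Payments per assessment, monitoring of adherence, and asking treatment drop-outs for the post-intervention and 6-month assessments should all reduce loss. Dropout is also openly listed as a limitation with consequences for effectiveness, so the article does not ignore the problem. But the request to treatment drop-outs does not name t1, and reducing loss is not the same as having none.
- **Mixed models use incomplete data.** The Data analysis section specifies multilevel mixed modelling. This helps adolescents who have some later score. Someone with only a baseline score adds almost nothing to the t1 contrast.

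A reader might go further and infer that the main models are complete-case analyses under an intention-to-treat label, because the article names a single time point (t1, or t4 and t5) as the dependent variable. The document does not establish that. It states no rule for missing data, which a fuller protocol or analysis plan may contain, and the section on sequencing refers to marginal means from a linear mixed model used to graph symptoms over time. That is compatible with a repeated-measures model.

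**Conclusion.** The point holds as a wrong rationale and an unsupported power statement. The 52, 1.22 and 64 are all correct on their inputs; the fault is not arithmetic. What is wrong is the claim that intention-to-treat makes a dropout allowance unnecessary, made in Sample size and echoed in Strengths and limitations, alongside the plan's own expectation of high dropout from assessments.

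Power of at least 0.80 at d = 0.33 holds only if practically all t1 scores are observed. The loss is slight at 5% missing (0.783–0.788), noticeable at 10% (0.761–0.770) and material at 20% to 30% (0.711–0.731 down to 0.653–0.683). These figures rest on assumed rates, on the plan's r, ICC, m and cv, and on missing scores adding nothing to the t1 contrast. The article does not support naming one of these rates as the expected one, nor saying that the analyses discard incomplete cases.

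**What to change.** 1. In Sample size, strike the clause that gives intention-to-treat as the reason for no allowance. Say instead that the sample was not enlarged for dropout, and give power and detectable d at an explicit expected t1 loss. For example, if 20% is the expected loss: about 71–73% power for d = 0.33, or 80% power for d of 0.36–0.37.
2. In Strengths and limitations, strike the matching sentence that intention-to-treat prevents the effect of dropout, and bring the well-powered statement into line with the restated figures.
3. Only if the t1, t4 and t5 contrasts are meant to come from single-time-point models: use a likelihood-based longitudinal mixed model, or multiple imputation, so that adolescents with any follow-up score contribute. The CDI-2 is used in a 28-item and a 12-item version. If the version differs by time point, score it on the items common to both before modelling it jointly. This step will not recover t1 information for adolescents with baseline data only, so it does not replace the restated power.

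The cost of items 1 and 2 is wording and a less favourable stated power. Item 3, where it applies, is a change of analysis. None of them needs more participants or more data.

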### The program

The prevention program is designed for indicated prevention and will be offered in groups of about five adolescents. The program is developed by the researchers themselves, in close collaboration with CBT-therapists and experts in the field. For each of the four most commonly used CBT-components a module of three sessions is developed; one module with three sessions of cognitive restructuring (CR), one module with three sessions of behavioural activation (BA), one module with three sessions of problem solving (PS) and one module with three sessions of relaxation (RE). The modules were developed based on cognitive and behavioural theories, a taxonomy that describes the techniques that diverse CBT-components should comprise [22], current Dutch CBT-protocols (e.g., The D(o) epression course, [41]; Op Volle Kracht, [43]) and the MATCH-ADTC [46]. In each step of this developing process, a group of certified CBT-therapists and experts in the field was consulted. Also [name] was consulted during the process (December 2016).

The program consists of twelve sessions (4 components * 3 sessions) of 45–60 min each. Prior to the program an introductory meeting will take place which lasts 30 min. The program takes place at the participating schools directly after school, one to two times a week (depending on holidays and schools’ preferences). It will be provided by certified alumni pedagogics/psychology, who are trained in two-and a half days and supervised by psychologists. Treatment adherence of participants will be monitored by the therapists and stimulated if necessary.

### Study outcome measures

For an elaborate overview of study outcome measures, see Table 2**.**

**Table 2 Tab2:** Overview of study outcome measures

Type of variable	Domain/Concept	Instrument	Items	Source			Assessment			
				A	P	T	*t* _*0*_	*t*_*1*_-*t*_*3*_	*t* _*4*_	*t* _*5*_
Primary outcome	Depressive symptoms	CDI-2 (FV) CDI-2 (SV)	28 12	x x			x	x	x	x
Secondary outcome	Depressive symptoms	NRS for core symptoms of depression ^a^	3	x			x	x	x	x
		CDI-2 parent version	17		x		x		x	x
	Depression diagnosis	K-SADS affective disorders		x	x		x		x	x
	Top three problems	TP measure^a^	3	x			x	x	x	x
	Suicidal ideation (if score 2 on item 8 CDI-2)	VOZZ suicide items	8	x			x	x	x	x
	Health-related quality of life	EQ-5D-Y	6	x	x		x		x	x
Cost-effectiveness	Healthcare costs	Cost diary	21		x		x		x	x
Moderators	Depression severity	K-SADS		x	x		x		x	x
	Comorbidity	BPM	19	x	x		x		x	x
	Demographics adolescent/parent/therapist			x	x	x	x			
Mediators	Negative cognitive errors	CNCEQ-R (FV) CNCEQ-R (SV)	16 5	x x			x	x	x	x
	Behavioural activation	BADS (FV) BADS (SV)	25 9	x x			x	x	x	x
	Problem solving skills	SPSI-R	10	x			x	x	x	x
	Relaxation	PSS-10	10	x			x	x	x	x
		NRS for relaxation	1	x			x	x	x	x
Treatment characteristics	Current and previous treatment	VEHI	6	x			x			x
	Expectancy of treatment	PETS	7	x			x			
	Therapeutic alliance	TASC-r	12	x		x		x	x	
	Groups cohesion	GCQ-s	12	x				x	x	
	Cooperation with treatment	CWT	5			x		x	x	
	Satisfaction treatment	SSS	3	x					x	

*Abbreviations*: *A* Adolescent, *FV* Full-length version, *NRS* Numerical Rating Scale, *P* Parents, *SV* Short version, *T* Therapist, *t*_*0*_ Baseline assessment, *t*_*1–3*_ Intermediate assessments, *t*_*4*_ Post-assessment, *t*_*5*_ 6-month follow-up assessment.

^a^These questionnaires will also be administered prior to each session

### Screening measures

To assess the eligibility to participate, adolescents will be screened for *depressive symptoms* using a self-report questionnaire, the CDI-2 [50] which includes 28 items. All items offer three graded options from 0 to 2, of which one is chosen (e.g., 0 = “I am sad once a while”, 1 = “I am sad many times”, 2 = “I am sad all the time”), with higher scores indicating more depressive symptoms according to the adolescent. Item 8 measures the presence of *suicidal ideation* (0 = “I don’t think about ending my life”, 1= “I think about ending my life, but I would never do”, 2 = “I want to end my life”= 2). In case a participant scores 2 on this item, the suicide items of the VOZZ [51] will be administered to assess suicidal ideation more extensively. The VOZZ consists of 39 items of which 8 items measure past and present suicidality, therefore only these items will be administered. Items are rated on a 5-point scale, ranging from “never/no day” to “very often/every day”, with higher scores indicating more self-reported suicidal ideation.

### Primary outcome measure

The degree of *depressive symptoms* in adolescents will be measured with the CDI-2 [50], as described in the previous section. Both the full-length version (28 items) and the short version (12 items) will be used. The full-length version has good internal consistency, test-retest reliability and convergent validity [50]. For the short 12-item version, Dutch psychometric properties have not been studied yet. Based on the dataset of the Dutch CDI-2 manual, we calculated the internal consistency of the short 12-version in the general population of adolescents, which was acceptable (α = .76, *n* = 2246) [50].

### Secondary outcome measures

In addition to the CDI-2, three Numerical Rating Scales will be used to measure the *core symptoms of depression* (depressed/irritable mood and loss of interest or pleasure in nearly all activities) in the last week, ranging from 0 to 10. The first scale focuses on depressed mood (0 = “very depressed”, 10 = “very happy”), the second on irritable mood (0 = “very irritated”, 10 = “very relaxed”) and the third on loss of interest or pleasure (0 = “no pleasure at all”, 10 = “a lot of pleasure”). The scales are developed by the researchers themselves, based on the core symptoms of Major Depressive Disorder specified in the Diagnostic and Statistical Manual of Mental Disorders, Fourth Edition, Text Revision (DSM-IV-TR; [54]).

The degree of *depressive symptoms of the adolescent according to the parent* will be measured with the CDI-2 parent version that contains 17 items [50]. Items are rated on a 4-point scale ranging from “not at all” to “almost always”, with higher scores indicating more depressive symptoms according to the parent. The internal consistency and convergent validity are qualified as good [8].

The presence of a *depression diagnosis* will be measured by a semi-structured diagnostic interview, the Kiddie-Schedule for Affective Disorders and Schizophrenia, present and lifetime version (K-SADS; [55, 56]). The view of the adolescent, the parent and the independent clinician will be taken into account. Only the section of affective disorders will be assessed. In previous research, the concurrent and convergent validity of the K-SADS was supported [55, 57], the interrater agreement was high (range: 93 to 100%) and test-retest reliability was excellent (.77 to 1.00) [55]. The K-SADS will be assessed by independent master students pedagogics/psychology and research assistants who will be trained and supervised in the K-SADS and depressive symptomatology. They will be blind to the allocation of the participants.

The *top three problems* of adolescents will be measured with the Top Problems (TP) measure [58]. It measures adolescents’ problems of greatest concern at baseline assessment. Adolescents are asked to list problems, they are concerned about most. When the list is complete, the interviewer will obtain severity ratings for each problem (“How big of a problem is this for you?”) on a scale ranging from 0 (not at all) to 10 (very, very much). Than the interviewer will repeat all problems that the adolescent has identified and asks which one “is the biggest problem right now?”. The problem identified will be assigned as rank 1; then the interviewer asks for the next biggest problem (rank 2), and the next (rank 3). This will result in a ranked list of the top three problems. In our study, the top three problems will be requested once (at baseline), by independent master students pedagogics/psychology and research assistants who are blind to the allocation of the participants. At subsequent assessments, only the severity of the top three problems will be rated by the adolescent. Psychometric properties of the TP measure are qualified as good [58].

As described in the previous section, *suicidal ideation* will be measured with item 8 of the CDI-2 and 8 items of the VOZZ [51]. The VOZZ has good internal consistency and test-retest reliability [51].

The Dutch version of the EQ-5D-Y [59] will be used to establish *health-related quality of life* as expressed in quality adjusted life years (QALYs), with parallel forms for adolescent and parent report. The questionnaire comprises five dimensions: Mobility, Self-care, Usual activities, Pain/discomfort and Anxiety/depression. Each dimension has three levels: no problems (1), some problems (2) and a lot of problems (3), with higher scores indicating a lower quality of life of the adolescent. The questionnaire also comprises a Visual Analogue Scale (ranging from 0 to 100) that records the adolescents’ health, where 0 is labelled as “worst imaginable health state” and 100 as “best imaginable health state”. The reliability and validity of the questionnaire have been established [60].

*Healthcare costs* will be measured by registration of health care usage and costs of the last three months in a cost diary reported by the parent, which has been used in previous research on anxiety and depression [9, 61, 62]. Health care usage and costs that will be registered are direct health care costs (e.g., psychologist, general practitioner and medication), direct non-health care costs (e.g., informal care), indirect costs (monetary value of production losses caused by absence and reduced productivity and school) and out-of-pocket costs (e.g., own contribution and transport costs). Costs will be calculated from the mental health care system’s perspective and from a societal perspective.

### Moderators

The *severity of the depression* will be rated on the basis of the number of depressive symptoms (five to six symptoms: mildly depressed, six to eight symptoms: moderately depressed, eight to nine symptoms: severely depressed), the nature of symptoms (when suicidal ideation is present, the severity will be rated as severe) and the interference with daily functioning in different contexts such as at school, at home and in social life (one life area: mildly depressed, two to three life areas: moderately depressed, four life areas: severely depressed) as suggested by the Dutch guideline for depression in youth [63]. The rating will be done by independent master students pedagogics/psychology and research assistants, who are blind to the allocation of the participants, based on the results of the K-SADS interview [55, 56].

*Comorbidity* will be assessed with the Brief Problem Monitor [1], with parallel forms for adolescent and parent report. The questionnaire contains 19 items and comprises three scales: Internalizing, Externalizing and Attention Problems. Items are rated on a 3-point scale ranging from “not true” to “very true”, with higher scores indicating more comorbid problems. Psychometric properties are qualified as good [64, 65].

*Demographic information* of the adolescent, parents and therapist will be gathered by adding questions to the self-report questionnaires about gender, age, ethnicity and education level.

### Mediators

*Negative cognitive errors* will be measured with the Children’s Negative Cognitive Errors Questionnaire-Revised (CNCEQ-R; [66]), to track changes in the assumed mediator of cognitive restructuring, namely negative cognitive errors. The questionnaire comprises 16 items, which are divided into five categories: Underestimation of the ability to cope, Personalizing without mind reading, Mind reading, Selective abstraction and Overgeneralizing. Items are rated on a 5-point scale ranging from “not at all like I would think” to “almost exactly like I would think”, with higher scores indicating more self-reported negative cognitive errors. For the total score, high test-retest reliability and good internal consistency have been established [66]. Because of limited time at the intermediate assessments (*t*_*1*_ - *t*_*3*_), we will only administer five items of the questionnaire (item 1, 4, 5, 9 and 14). For each subscale we selected the item with the highest loading based on the factor analysis of Maric et al. [66].

*Behavioural activation* will be assessed with the Behavioral Activation for Depression Scale (BADS; [67]), to measure changes in activation and avoidance. The self-report questionnaire contains four scales: Activation, Avoidance/rumination, Work/school impairment and Social impairment. Both the full-length (25 items) and the short version (9 items) will be used. The short version only contains the scales Activation and Avoidance. Items are rated on a 7-point scale ranging from “not at all” to “completely”. For all subscales, higher scores mean greater intensity on a particular dimension (e.g., the higher the score on the Activation subscale, the more activation). Psychometric properties for both the full-length and the short version are qualified as acceptable to good [68, 69].

*Problem solving skills* will be assessed with the 10-item version of the Social Problem Solving Inventory-Revised (SPSI-R; [70]), to track changes in someone’s approach toward problem solving in daily life. Items relate to five subscales: Positive problem orientation, Negative problem orientation, Rational problem solving, Impulsivity/carelessness style and Avoidance style. Items on this self-report questionnaire are rated on a 5-point scale ranging from “not at all true” to “extremely true of me”. For all subscales, higher scores reflect greater intensity on a particular dimension (e.g., the higher the score on the Positive problem orientation subscale, the more positive problem orientation someone reports). Psychometric properties have demonstrated good reliability and validity [71].

*Relaxation* will be measured with the Perceived Stress Scale (PSS-10; [72]), to measure changes in the degree to which someone appraises situations as stressful. The scale consists of 10 items, which are rated on a 5-point scale ranging from “never” to “very often”, with higher scores indicating more self-reported stress. Psychometric properties are qualified as acceptable [73]. In addition to the PSS-10, a Numerical Rating Scale from 0 to 10 will be used to measure relaxation in the last week, developed by the researchers themselves (0 = “very stressed”, 10 = “very relaxed”).

